#### Stage 5: Randomization

Random allocation will be conducted by a statistician independent of the study, who will use an electronic system to randomly allocate the two clusters to intervention (IG) and control group (CG). Both the researchers (except the principal investigator) and the data analyst will not be aware of which cluster will be the intervention group and which one will be the control group. This *blinding* reduces the influence that researchers may have when collecting the quantitative datasets from the community clusters [40] and any influence that the data analyst will have when analyzing the same data sets. The 25 potential interventionists in the allocated intervention cluster will receive the training and the 9-cell bereavement tool, as explained in Stage 6 below. The control group will be waitlisted to receive the intervention at the end of the study (following final endline data collection point).

#### Stage 6: Intervention

The 25 lay community members in the cluster randomized to be the intervention group (IG) will take part in the intervention of the 9-cell bereavement tool. The ex-bereavement service coordinator and trainer, responsible for the development of the 9-cell bereavement tool, will administer the 9-cell bereavement tool with assistance and translation from one Island Hospice Healthcare (IHH) social worker. Before the intervention, the trainer will provide intensive pre-intervention preparation with the IHH social worker in order to transfer skills to IHH as a secondary benefit of the study. IHH will support the administration of the 9-cell tool in the identified communities.

The 9-cell bereavement tool is administered in a 7-h (1 day) session. Community lay caregivers are an appropriate target as social support can improve grief and bereavement outcomes [41, 42].

It assesses personal feelings in relation to bereavement, identifies judgmental attitudes, inappropriate religious tenets, lack of understanding, effects of family, and community support. The 9-cell bereavement tool places the uniquely personal journey of grief firmly within the social setting in which grief is processed; how to ensure a better fit for the grieving individual within their society; is particularly useful in multicultural settings; and was developed from experience from local bereavement beliefs and practices.

The overall process of implementing the 9-cell bereavement tool:Builds on people’s existing knowledge and experienceModels an open-minded and non-judgmental approachRecognizes great diversity in grief experiences in individuals, genders, families, cultures, and faithsEncourages intervention participants to listen to others while helping them to break down barriers of previously held beliefs about grief

Transport fees, incentives, and refreshments will be provided during the intervention as in the data collection phase of the study.

#### Stage 8: Endline data collection (T2)

At T2 (endline data collection; week 27 or 3 months post-midline), all trial participants will complete the questionnaires following procedures for the quantitative data collection described above. An additional data collection process will occur with the intervention group (IG). As they complete the final endline questionnaire, 10 to 15 participants will be purposively recruited into a focus group (FGD#4 as indicated in Fig. 1—the study flow chart). Purposive sampling will guide in recruiting at least an equal number per gender and age. In the group discussion, the principal investigator will share information about the intervention to the intervention group trial participants. Following the explanation, the trial participants, will join in a discussion centered on why they agreed to be in the study, what it was like for them, how often they saw the interventionist who recruited them into the study, what they discussed regarding bereavement, what they learnt to do or feel differently following the discussions, who initiated the discussions they had with the interventionists, any negative and or positive thoughts or actions that followed, discussions with others outside of the intervention, how the study helped, and if they felt they needed extra support they may require following the end of the study.

Once baseline, midline, and endline data collection, including the focus group discussions (FGD 1, 2, and 4, as indicated in the study flow chart in Fig. 1), a separate focus group discussion (FGD # 3) will be held with interventionists to assess their experience in interacting with the bereaved within their communities. This topic guide will ask questions around how they maintained the conversations with regard to bereavement with those in their communities, was it sustainable, were there any changes they noticed from the community in their renewed communication, do people actively seek them out, are they sort after, what do people want to discuss when they see them, are there self-described gains and if so what are they, will they use any of the lessons learned going forward, what will they use, what do they need to sustain this, and does anyone outside the trial ask for support from them?

## Data management

### Confidentiality

All completed consent forms will be kept in a locked room and cupboard at IHH, the local supporting organization. Only recognized research team members will have access. All analysis will be performed and saved on a password-protected laptop. No names will be included on the data collected; code/questionnaire numbers will have code numbers allocated to each respondent/participant’s responses. Questionnaires will be stored separately from the information and consent forms. Only the questionnaires will have the study ID numbers, not the information and consent forms. This further reduces any cross analysis.

### Compensation

All participants will be reimbursed for public transport to the study sites and will be provided with light refreshments at the venue. Participants will receive a small token of appreciation, valued at approximately USD3, to compensate them for the time taken to participate in the study. For their convenience, data collection will take place within the respective communities where the participants reside. Transport fare of an equivalent of USD2 will be provided to each participant.

## Data monitoring

Data monitoring (recruitment, retention, adverse events) will be reported to the Steering Committee meetings (chaired by the Chief Investigator, [name]) by the local principal investigator ([name]) for review.

## Data analysis

Quantitative data will be entered into a study-specific excel spreadsheet prior to import to SPSS for analysis.

In terms of recruitment, we will calculate the proportion of the target sample achieved for community lay interventionists and trial participants.

With respect to retention, we will calculate the proportion of potential trainees recruited who attended the full day training, and the proportion who remained active in bereavement support until trial end. We will report the proportion of trial participants who participate in T0 (baseline of week 0), T1 (midline at week 14 or 3 months post-baseline), and T2 (at week 27 or 3 months post-midline) data collection.

In terms of the outcome data, we will measure data completeness at each timepoint. We will plot data to check for floor and ceiling effects (to help us inform primary outcome selection), report data completeness, and plot means/standard deviations or medians and IQR (depending on data normality/symmetry of distribution) for each timepoint. We will appraise the selected outcome measures in terms of the qualitative explanation of perceived intervention benefits (and potential unintended consequences).

We will estimate potential treatment effect size using longitudinal methods for non-parametric data (no interim analysis), using an appropriate method (e.g., ANCOVA adjusting for baseline scores, with 95% confidence intervals). With regard to contamination, if we find that 8 km was a sufficient distance to minimize contamination, then we will (in full trial development) determine clusters that meet this criterion, which appears possible within Zimbabwe.

Verbatim transcripts of the individual and focus group interview data will be imported into NVIVO for analysis using the framework approach [44]. The trial participant and interventionist datasets will be analyzed separately. The thematic analysis will populate the framework by case analysis to generate themes, with the matrix permitting between-case comparison. Data will be integrated by appraising the quantitative outcomes in light of the qualitative description, with parity between the data types.

We will measure success in terms of our a priori criteria stated above, and if necessary refine methods by integrating the qualitative and quantitative data. If success criteria have not been met, refinements will aim to improve the design.

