**Methods/design:**

This feasibility cluster randomized trial with embedded qualitative interviews will be conducted in two comparable neighborhoods in Zimbabwe. Community leaders from each neighborhood will identify 25 potential community lay bereavement supporters, each of whom will recruit 2–3 bereaved community members into the trial. The intervention will be randomly allocated to one community, and the second community will form a wait-list control (*n* ≥ 75 in each community cluster). Recruitment is estimated to take place over 3 weeks. Measures at T0 (baseline, i.e., week 0), T1 (midline, i.e., week 14 or 3 months post-baseline) and T2 (endline, i.e., week 27 or 3 months post-midline) will address mental health, social support, and levels of grief per individual. Qualitative data will describe lay supporters’ views of intervention training and delivery, and participants’ experience of bereavement support.

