## Methods

### Aim and objectives

The aims of this study are to assess the feasibility of implementing the 9-cell bereavement tool at the community level and to determine the feasibility of evaluating the intervention using a cluster randomized control trial design.

The objectives are (i) to determine the feasibility of conducting a randomized cluster trial in terms of recruitment and retention; (ii) to assess the feasibility of implementing the 9-cell bereavement tool; (iii) to determine whether there would be contamination between the clusters; (iv) to assess the acceptability and completeness of measures and data; (v) to identify trial participants’ views and experience of the intervention and its mechanisms of action; (vi) to estimate potential effect size; and (vii) to determine whether a full trial is warranted.

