### Feasibility questions and success criteria

We will seek to answer the following research questions: (1) will we be able to recruit at least 75% of the suggested sample size of interventionists and trial participants interventionists within 3 weeks? In order to meet proposed trial timelines, we suggest trial recruitment criteria of recruiting community leaders within 1 week; interventionists within 1 week and the trial participants within 1 week; giving a total recruitment period of 3 weeks. (2) Will we be able to retain at least 75% of both the trial participants and the interventionists in the total duration of the study? (3) Can we deliver the 9-cell bereavement intervention as intended? (4) Will the processes of a randomized cluster trial be possible? (5) Does process data suggest that the anticipated effect is likely?

There is a paucity of guidance on setting progression criteria for feasibility and pilot trials [25]. Therefore, we draw on the MRC guidance that such criteria should be judged in light of all study findings and used to refine study design. Our recruitment and retention criterion of 75% was set in light of published feasibility trial criteria and reflects the nature of our population (i.e., they are community-dwelling bereaved individuals without any known serious health conditions and so we anticipate high retention).

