### Setting

This study will be conducted in Chitungwiza, a city bordering the capital city of Zimbabwe. A local supporting organization for this study, Island Hospice and Healthcare (IHH), has been involved in community work in Chitungwiza for the past 15 years engaging community groups, community leaders, non-governmental organizations (NGOs), churches, and government ministries.

Two broadly similar communities within Chitungwiza have been selected; one will act as the intervention group (IG) and the other as the control group (CG). Chitungwiza is densely populated with a large surface area, which greatly reduces potential contamination between the two selected intervention and control areas. Figure 2 provides the map of Chitungwiza; one community cluster is in the north-west section and the second is in the south-east, therefore reducing the likelihood of contamination. They have similar socio-demographic characteristics and value systems, with the economy being largely supported by informal trade and falling under the same traditional territory and health administration. The two communities selected within Chitungwiza are about 8 km apart. Through discussion with local stakeholders, 8 km is anticipated to be adequate distance and corresponding density to reduce possible contamination between the two clusters. However, as an added precaution, the control group will be asked at midline and at endline to establish whether they have visited the community where the intervention took place and if they had a discussion with any community member who received the intervention.

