## Discussion

This study will assess the feasibility of implementing the 9-cell bereavement tool at a community level and to determine the feasibility of evaluating the intervention using a cluster randomized control trial design. This will enable us to determine optimal successful design for a full trial in an area that is currently neglected in the literature but has an enormous potential public health benefit. This protocol will enable us to provide a transparent analysis of the feasibility trial and reduce reporting bias [45]. We will appraise the results against the stated success criteria.

To reduce reporting bias, findings will be submitted for publication in peer-reviewed journals and be shared through the ethics review committees for wider distribution. Study results will guide a national bereavement strategy, promoting intervention dissemination across communities in Zimbabwe. Positive results from this study would support intervention rollout to many other African countries and training related to the feasibility study, and its methods will be shared regionally with other researchers in the same program.

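### With one community per arm, the planned effect estimate cannot be separated from the difference between the two communities, and an individual-level 95% CI leaves that error out

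*Protocol article*

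**What the plan says.** The abstract gives the design: "The intervention will be randomly allocated to one community, and the second community will form a wait-list control". Stage 5 (Randomization) says that an independent statistician will "randomly allocate the two clusters to intervention (IG) and control group (CG"). The Setting section says of the same two communities that "one will act as the intervention group (IG) and the other as the control group (CG"). Comparability rests on a qualitative statement: "Two broadly similar communities within Chitungwiza have been selected".

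The last-but-one objective under Aim and objectives is "vi) to estimate potential effect size". The Data analysis section carries it out with longitudinal methods, "using an appropriate method (e.g., ANCOVA adjusting for baseline scores, with 95% confidence intervals"). It names no allowance for community. Nowhere does the article say that arm and community coincide, or that the interval excludes variation between communities. The Study design section does recognise that delivery is at community level and that a full trial would need cluster randomisation.

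The Discussion adds: "Positive results from this study would support intervention rollout to many other African countries".

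**The concern.** With one cluster per arm, a between-arm difference is also a between-community difference. Anything that affects bereaved people in one community but not the other over the 27 weeks enters the arm coefficient. An interval built from variation between individuals treats that component as zero. The result would appear in print as a treatment effect with a 95% CI, although the interval has 95% coverage only if communities do not differ at all. A later team could take the estimate and its apparent precision at face value when planning the full trial.

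**Working it through.** **Inputs from the protocol.** There are two clusters, one per arm (abstract, Setting, Stage 5). The number per cluster is inconsistent: at least 75 (abstract), a target of 50 and a reach of 75 with no unit (Sample size), and 25 per community (Stage 4). Recruitment arithmetic gives 25 × 2 = 50 to 25 × 3 = 75 per community. The check is therefore run at m = 25, 50 and 75. The protocol gives no power calculation, SD or ICC, so it has no figure of its own to reproduce.

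**Assumptions.** ICC between communities of 0.01, 0.02, 0.05 and 0.10. For ANCOVA, an individual baseline–outcome correlation of 0.5 and a correlation of community effects over time of 0.5, 0.8 or 1.0.

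**Step 1, structure.** Cluster-level residual degrees of freedom = clusters − arms = 2 − 2 = 0. The between-community variance cannot be estimated. This step needs no assumed ICC.

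**Step 2, unadjusted comparison, in units of the total SD.**

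- SE ignoring community = √(2(1 − ICC)/m)
- Actual SE = √(2[ICC + (1 − ICC)/m])
- Actual coverage = 2Φ(1.96 × SE ignoring community / actual SE) − 1

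Example, m = 75 and ICC = 0.05: √(2 × 0.95/75) = 0.159; √(2[0.05 + 0.95/75]) = 0.354; 1.96 × 0.159/0.354 = 0.88; coverage 62%.

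| Assumed ICC | Coverage, m = 75 | m = 50 | m = 25 | Half-width at m = 75: reported / needed (SD) |
|---|---|---|---|---|
| 0.01 | 86% | 89% | 92% | 0.32 / 0.42 |
| 0.02 | 78% | 83% | 89% | 0.32 / 0.50 |
| 0.05 | 62% | 70% | 80% | 0.31 / 0.69 |
| 0.10 | 48% | 56% | 69% | 0.30 / 0.93 |

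More participants do not cure this. As m grows, the actual SE cannot fall below √(2 × ICC) = 0.14, 0.20, 0.32 and 0.45 SD.

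**Step 3, baseline-adjusted ANCOVA.** Simulated with no treatment effect, 3,000 runs per setting, m = 75. Ranges run over the three community-effect correlations.

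| Assumed ICC | Coverage | Half-width: reported / needed (SD) |
|---|---|---|
| 0.01 | 87–93% | 0.28 / 0.30–0.36 |
| 0.02 | 78–90% | 0.28 / 0.34–0.44 |
| 0.05 | 62–81% | 0.28 / 0.41–0.61 |
| 0.10 | 47–71% | 0.27 / 0.51–0.81 |

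At ICC = 0 the same simulation returns 94–95%, as it should. Baseline adjustment helps most when community effects are perfectly stable (the upper end of each range), but even then coverage falls short of 95%.

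**The case against.** The strongest reply is that this is a feasibility trial. One cluster per arm is acceptable for recruitment, retention, completeness and contamination, and the effect size is one of seven objectives, called only potential. ANCOVA is an example, so an analysis plan may choose another method. The treated community is chosen at random.

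Much of this stands. The feasibility objectives do not depend on the estimate. Random choice makes it unbiased over repeated allocations, so the defect is an error that cannot be quantified, not a systematic bias. The choice of method, however, does not rescue it: no individual-level, longitudinal or mixed model can separate two things that coincide in the data.

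Several stronger readings are tempting, but the protocol does not support them:

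- A reader might infer that the estimate answers the fifth feasibility question. That question reads "5) Does process data suggest that the anticipated effect is likely" and so concerns process data, not the ANCOVA.
- A reader might infer that the estimate will size the full trial. The protocol does not say so. Success is judged on the stated feasibility criteria, none of which sets a threshold on the effect or its interval. The objective on whether to proceed could draw on it, and nothing rules that out.
- A reader might object that no between-community ICC can be obtained. That is true, but the protocol never promises one.
- A reader might infer that the rollout sentence rests on the ANCOVA. What counts as positive is undefined there and may mean feasibility results. The sentence still goes too far, because feasibility in two neighbourhoods of one city does not support rollout elsewhere.

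**Conclusion.** The point holds for the effect estimate and its interval. As written, the Data analysis section would report as a treatment effect a quantity that includes the community difference left after baseline adjustment, with an interval that omits between-community error. That conclusion follows from the design alone.

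Its size rests on assumed ICCs that this trial cannot check. With 75 per community, the shortfall under ANCOVA runs from slight (93% coverage at ICC 0.01 with stable community effects) to severe (47% at ICC 0.10 with a community-effect correlation of 0.5). With fewer per community, coverage is less poor, only because the reported interval is wider. No single coverage figure should be quoted as the true one.

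The trial's main purpose, and the fifth feasibility question, are not affected.

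**What to change.** - **Aim and objectives, and Data analysis:** report each community's change across T0, T1 and T2 descriptively for the SSQ, MSSS and TRIG, with SDs and baseline–follow-up correlations. The effect-size objective may stay if it is qualified as below.
- **Any between-arm figure:** label it as the difference between two communities, and state that its CI excludes between-community variance. Show the interval under assumed ICCs, for example 0.01 to 0.10, beside the individual-level one.
- **Use:** state that the figure will not be taken as the treatment effect for sizing a full trial.
- **Discussion:** limit the conclusion to the case for a full trial, and drop the step to rollout.

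The cost is wording and a short sensitivity table, with no extra data. The downside is that the feasibility trial yields no headline effect size. The conflicting numbers per community should be reconciled at the same time, since the width of any interval depends on them.

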## Discussion

This study will assess the feasibility of implementing the 9-cell bereavement tool at a community level and to determine the feasibility of evaluating the intervention using a cluster randomized control trial design. This will enable us to determine optimal successful design for a full trial in an area that is currently neglected in the literature but has an enormous potential public health benefit. This protocol will enable us to provide a transparent analysis of the feasibility trial and reduce reporting bias [45]. We will appraise the results against the stated success criteria.

To reduce reporting bias, findings will be submitted for publication in peer-reviewed journals and be shared through the ethics review committees for wider distribution. Study results will guide a national bereavement strategy, promoting intervention dissemination across communities in Zimbabwe. Positive results from this study would support intervention rollout to many other African countries and training related to the feasibility study, and its methods will be shared regionally with other researchers in the same program.

